**Fig 3 pone.0272481.g003:**
[figure not shown]
Integrated microsimulation model (MS).

*Step 1*. The creation of a synthetic cohort for 2019–2030 using the demographic, socioeconomic and exposure variables as an extension of the big retrospective cohort of 2001–2018 analysis from the previous objectives. For each individual, we will simulate changes in socioeconomic variables over time based on transition probabilities and consistent with different economic scenarios. We will simulate socioeconomic changes as a result of the current economic crisis related to the COVID-19, modelling increases in poverty rates at different pace, intensity and length, together with other relevant social drivers of mental illnesses. Several BFP coverage responses will be tested through three main scenarios to reflect different economic conditions: a) a fiscal austerity scenario assuming a reduction of BFP coverage; b) a stable scenario assuming BFP coverage level is maintained at the pre-economic crisis level; and c) an enhanced coverage scenario, in which BFP is increased to protect all the newly poor individuals from the economic recession. Targeting social determinants, using cash transfer programs, could be important tools to limit hospitalizations from mental illness and suicide among youth, predicted to rise in the aftermath of economic recession consequent to the COVID-19 pandemic.

*Step 2*. The estimation of hospitalizations incidence and mortality for 2019–2030 using the individual-level values of each variable of the synthetic cohort and their effects estimates from the previous retrospective analyses. The microsimulation modelling will follow ISPOR guidelines [40] for each outcome and each scenario, 10,000 Monte Carlo simulations will be performed obtaining the Predictive Intervals of each estimate. The external validation will be performed comparing hospitalizations and mortality estimates from MS models for all country in 2001–2018 with official estimates from the Ministry of Health and from UN agencies, which are adjusted for underreporting and data quality. The linear regression of predicted versus observed values and the proportion of variance (R2) explained will be assessed, and we will verify that all observed values will be included in the 95% CIs of the simulation estimates, among other validation criteria [38–40]. Scenarios will be compared along with ratios of incidence and mortality, and the number of averted cases and deaths.

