#### Data and measures

Datasets, variables, and sample sizes.

***100 Million Brazilian Cohort*.** We will analyze a cohort of subjects registered in Unified Registry for Social Programs (CadÚnico). The CadÚnico is a data collection and storage system that contains individual records with demographic and socioeconomic information on the poorer half of the Brazilian population (n = 114,007,705). Anyone who meets the eligibility criteria can be registered by visiting one of the Centers for Social Assistance (CRAS) or be registered at home, as social workers visit households periodically to identify and register eligible individuals. The criteria to be eligible for CadÚnico registration are: having a monthly family income per capita of half the minimum salary in Brazil (778 reals in 2015) or less; or having a total family income (monthly) of up to three minimum salaries. The CadÚnico contains information about housing conditions, income and demographic characteristics of all the members of a registered family [26].

***Bolsa Familia Program (BFP)*.** The Brazilian Cash Transfer Program (BFP) is the largest poverty alleviation program in the world, with about 46 million people having received the benefit up to 2015. It has three aims: income supplement guarantee for immediate relief of extreme poverty (people who live with up to 70 reals per capita) [27]; access to public services (improving education, health, and citizenship of families); and productive inclusion to increase the capacity and job opportunities, and income generation among the poorest families [28].

In 2014, the eligibility criteria for participation in the program (which is more stringent than the conditions for eligibility to register in CadÚnico) was having an income of less than 77 reals (14 USD) monthly per person or less than 154 reals in cases where there is a child, adolescent or pregnant woman in the family. The benefits were: “basic benefit”, 77 reals monthly, regardless of family composition; an extra 35 reals to families with a child or adolescent between 0–15 years, or a pregnant or nursing woman; and an extra 42 reals per adolescent from 16–17 years, in 2014. Families living in extreme poverty can accumulate all these “basic benefits” to a maximum of 1,332 reals per month (235 USD).

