Notifiable Diseases Information System (SINAN)	This dataset comprises compulsory notifiable diseases information and violence, emotional and physical, as well as suicide attempt.	Compulsory notifiable diseases, including occurrences reported for: self-inflicted violence (333,933), interpersonal violence (2,111,051), and intimate partner violence (433,664).	Individual sociodemographic and clinical data of suspected and confirmed cases of interpersonal and self-inflicted violence (suicide attempt and self-agression) and intimate partner violence. It also includes information regarding the perpetrator, such as relationship with the victim.
Demographic Census (IBGE)	Household census to collect information on all households and individuals in the country and characterize the Brazilian population in terms of its demography and socioeconomic characteristics.	All Brazilian municipalities (n = 5,670).	Population, fertility, mortality, migration, housing characteristics, characteristics of the neighbourhood, education, income, labour, social inequality (Gini index), Human Development Index (HDI), proportion of poor people, etc.

Besides information from BFP, from the CadÚnico, we will also access information from the Hospitalization Information System to identify hospitalizations from: (A) mood disorders (832,974); (B) anxiety; (C) psychosis (1,952,605); (D) prescribed or illicit drug abuse and dependence; (E) alcohol abuse and dependence; (F) alcohol-related liver, problem/chronic liver disease; (G) physical injuries (228,278); (H) attempted suicide (178,606); and (I) suicide (181,527), from 2001–2018. As well as violence notifications from the Brazilian Notification System for Health Surveillance and all cause-specific mortality data, collected from the Brazilian Mortality Information System. All hospitalization, notification, and mortality information data were obtained from the DATASUS held by the Brazilian Ministry of Health and transferred to CIDACS [29] for research purposes. All the data are recorded in the three systems using the International Classification of Diseases, 10th revision. Information systems have improved considerably in Brazil; an analysis of the adequacy of mortality data from 2003 to 2005 found high quality and reliable information [30]. All the data available at CIDACS/FIOCRUZ covers a period from 2001–2018; however, we may access more recent years when the study begins.

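### The microsimulation check asks that every observed value fall inside a 95% interval, which is not what 95% calibration implies, and the check called external uses the same years that supply the model

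*Protocol article*

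**What the plan says.** All of this is in the protocol article, Materials and methods, Analytic strategy, Aim 4, in the two-step description of the microsimulation.

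- **Intervals.** For each outcome and scenario, "10,000 Monte Carlo simulations will be performed obtaining the Predictive Intervals of each estimate".
- **Pass criterion.** After a regression of predicted on observed values and an R², the text continues: "we will verify that all observed values will be included in the 95% CIs of the simulation estimates". This check stands "among other validation criteria", and no consequence of failing it is given.
- **Comparison.** The validation is called external and consists of "comparing hospitalizations and mortality estimates from MS models for all country" for 2001–2018 with official figures from the Ministry of Health and UN agencies. Those figures are described as adjusted for underreporting.
- **Origin of the model.** Step 1 builds the synthetic cohort for 2019–2030 "as an extension of the big retrospective cohort" of 2001–2018. Step 2 takes its effect estimates from the study's own retrospective analyses of that cohort.
- **Population.** The Data and measures section describes the underlying registry as holding records "on the poorer half of the Brazilian population (n = 114,007,705").

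**The concern.** Three features of the check work against its purpose.

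1. A 95% predictive interval is built to miss about 5% of observations. Asking for no misses penalises a model whose intervals are right and favours one whose intervals are too wide.
2. The simulation is said to yield predictive intervals, but the observed values are tested against confidence intervals. An interval for the simulated mean need not contain anything like 95% of observed values, so the reader cannot tell which interval is to be used.
3. The years used to judge the model are the years used to estimate it. Agreement over 2001–2018 shows that the model reproduces its own period. It does not show that the model forecasts.

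At stake are the projections to 2030 and the scenario comparisons built on them, including averted cases and deaths. This check is the evidence offered that those projections, and the uncertainty around them, can be trusted.

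**Working it through.** The plan states no pass probability, so there is no figure to reproduce. The question is how often a perfectly calibrated model would satisfy the criterion.

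**Inputs**
- Miss rate per observed value: 0.05, from the 95% level.
- Years: 2001–2018, which is 18.
- Assumptions: one national value per year and one series per outcome. The article does not say that the comparison is annual.

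**Step 1: independent years.** P(all inside) = 0.95^18 = 0.397. The calibrated model therefore fails with probability 1 − 0.397 = 0.603. Expected misses are 18 × 0.05 = 0.9.

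**Step 2: correlated years.** Independence is unlikely, because the simulated years share coefficients and transition probabilities. Simulating stationary AR(1) standard normal errors over 18 years, 400,000 runs each, with limits ±1.96:

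| AR(1) correlation | P(all 18 inside) |
|---|---|
| 0 | 0.40 |
| 0.5 | 0.46 |
| 0.8 | 0.61 |
| 0.9 | 0.71 |
| 0.95 | 0.80 |
| 0.99 | 0.89 |

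The probability stays below 0.95 in every case.

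**Step 3: effect of over-wide intervals.** If intervals are m times too wide, coverage per value is 2Φ(1.96m) − 1, and P(all inside) is that figure to the power 18 (independent years).

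- m = 1: 0.950, giving 0.40
- m = 1.5: 0.9967, giving 0.94
- m = 2: 0.9999, giving 0.998

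A model that doubles its interval width passes almost surely.

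**Step 4: what a coverage rule would look like.** With misses distributed Binomial(18, 0.05), P(≥2) = 0.226, P(≥3) = 0.058 and P(≥4) = 0.011. Flagging at four or more misses would wrongly flag a calibrated model about 1% of the time if years are independent. In the AR(1) simulation of Step 2 that rate rises to about 3% at correlation 0.5 and about 9% at 0.9, because misses cluster. Simple binomial bounds are therefore too strict when years are correlated.

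**Step 5: if full inclusion is kept.** Joint 95% intervals are needed. Under independence the level per value is 0.95^(1/18) = 0.9972, or 99.72%.

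**Step 6: the years.** Effect estimates come from the 2001–2018 retrospective cohort, validation covers 2001–2018, and forecasts cover 2019–2030. No year in the validation lies outside the estimation period.

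**The case against.** The best reply is that this is one check among several, with no threshold and no stated consequence, so nothing in the article says that a model would be rejected for a single miss. That is right, and it limits the point: the criterion is wrong as a standard of calibration, but it is not a stated decision rule. The regression of predicted on observed values also already supplies an intercept and slope, so errors of level are not left untested. Neither that regression nor R², however, tests interval coverage.

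The switch from predictive to confidence intervals may be only a slip of wording, since the simulation output is named correctly shortly before. It still needs correcting, because the criterion depends on which interval is meant.

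A reader might infer more than the article supports:

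- **Nine outcomes by 18 years.** The outcome list in Aim 1 suggests 162 comparisons, for which a calibrated model would pass with probability 0.95^162 = 0.0002. The article does not say that the check runs over that grid, and the figure also needs independence throughout.
- **Half the country is left out.** The cohort covers the poorer half, while validation is national. But the article says that the model estimates are for the whole country, and the figure showing the model is not available here. How the cohort is extended may be set out there or in the full protocol, so silence in a condensed article does not show that the rest is unmodelled.
- **The comparator is simply the model's own data.** The article does say "All hospitalization, notification, and mortality information data were obtained from the DATASUS held by the Brazilian Ministry of Health", so the source overlaps in part. UN agency figures are also named, and their independence from Ministry data is not stated.
- **The inputs are unadjusted for underreporting.** The article does not say either way.

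**Conclusion.** The criterion should be changed. On 18 annual values for one outcome, a perfectly calibrated model meets it with probability about 0.40 if years are independent and about 0.46 to 0.89 for AR(1) correlation of 0.5 to 0.99, while wider intervals make it easier to meet. These figures rest on annual comparison and on the correlation range shown.

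The name of the interval must be made consistent. The word external is not earned as regards time, because estimation and validation share 2001–2018, so the check gives no evidence on forecasting beyond the data.

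The reach is limited to the Aim 4 forecasts and averted-case figures. The effect estimates of Aims 1 to 3 do not depend on this check. The documents do not support the further conclusions that the model omits the richer half of the country or that it is validated only against its own source.

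**What to change.** 1. Replace the full-inclusion criterion with a comparison of the empirical coverage of the 95% predictive intervals against 95%, with bounds that allow for correlation between years. If full inclusion is preferred, use joint 95% intervals instead.
2. Use the term predictive interval throughout.
3. Report interval width beside coverage, so that over-wide intervals are visible, and report the intercept and slope from the regression already planned.
4. Add a temporal hold-out: fit on earlier years, predict later years, and compare with events observed in the same linked cohort.
5. Describe the 2001–2018 national comparison as a same-period consistency check, and state that it is made on a matching population.

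The criterion should be fixed before the simulations are run. The cost is revised wording and one extra model fit, with no new data for the hold-out. Its limit is precision. If four years were held out, for example, a calibrated model would show no misses with probability 0.95^4 = 0.81, so a clean result for a single outcome says little about over-wide intervals. Coverage should therefore be read over all years and outcomes together.

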### Ethics consideration

This study will be conducted in accordance with Resolution N° 466/2012 of the National Health Council (CNS) and also complies with the international (Helsinki) research regulations. It was approved by two Ethics Committees of the: (i) Federal University of Bahia (application number: 1023107) and (ii) London School of Hygiene & Tropical Medicine (application number: 11581). The linkage of the databases will be carried out in a secure and protected environment, following a strict internal procedure to make sure data privacy and confidentiality [26]. A non-identified database will be used for the analyses, and this can only be accessed by authorized researchers, and once the data is obtained the analysis will be carried out following the CIDACS information security culture.

## Discussion

The study will use quasi-experimental approaches to assess the effect of social drivers on youth mental health-related hospitalizations and suicide, test mechanisms and pathways of a countrywide socioeconomic intervention, and examine the timing of the intervention during the life course, in a large sample of poor and impoverished Brazilian households. The BFP might result in positive impacts in all conditions related to difficulties in accessing health, education, social assistance, employment, and income, thus, improving youth mental health [4, 11, 19, 41]. The study will follow internationally recognized guidelines for conducting and disseminating the results of impact assessment studies, providing transparency in conducting data analysis, and greater comparability of results.

Suicide can be underreported due to stigma and therefore be misclassified when a family registers them. However, the process used to report violent deaths in Brazil reduces the chances of underreporting or misclassification. Suicide (and all deaths) were collected from the Brazilian Ministry of Health’s Mortality Information System (SIM) and the quality of this data has been previously recognized for having high-quality standards [30]. All death certificates in Brazil are completed following the "International Medical Certificate of Cause of Death Model", recommended by the World Health Assembly in 1948 (Brasil, 2001). Deaths due to external causes (suicide, homicide and accidents) are forwarded to the Medical Legal Institute (IML) (artigo 2º da Resolução CFM nº. 1.779/2005) where death certificates are issued and signed by an examining physician. Diagnoses are based on an autopsy, on the analyses of the circumstances in which the death occurred, personal history of the victim, and suicide risk factors [42].

Some limitations must be considered. The use of proxy in one of the four mechanisms proposed, physical injuries for impulsivity, can be a possible limitation in the analysis of mechanisms. However, assessment of impulsiveness and aggression in studies of risk factors for suicidal behavior, often depend on information from proxy informants, have been evaluated as robust [42]. Since both will be controlled by health care access, it is unlikely to have major differences between the group exposed and non-exposed. Quality of administrative data could also be challenging in these studies. Problems with quality can be related to problems with data collection and completeness of the data. However, most of the variables chosen for this project have less than 1% missing data. Most data that will be used for this proposal comes from CadÚnico that tend to be filled with precision due to the legal consequences on the beneficiaries. The forms are filled by trained interviewers, and missing information could result in not participating in the cash transfer program.

The large-scale data set will allow us to investigate comprehensively and in subpopulations the effects of BFP on youth mental health, as well test mechanisms of this effect. The use of these databases will allow exploring mental health outcomes with a high level of statistical power. The databases used in this study have national coverage, low under-registration, and some have already documented reliability. Therefore, this study will provide a comprehensive and representative analysis of the poor and extremely poor Brazilian population and reinforce the adequacy of these bases for epidemiological investigations. Results from this innovative project are expected to inform national efforts to prevent mental illnesses among youth from low-income communities in Brazil through the scale-up of economic interventions; our findings may also be relevant to other comparable middle income countries experiencing challenges, such as those resulting from the economic consequences of the COVID-19 pandemic, to address the burden of mental health problems among youth and reducing mental health disparities.

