Several drivers and mechanisms have been hypothesized to underlie the process of the association between cash transfer and better mental health outcomes, and there is also a bidirectional and intergenerational component. Haushofer and Shapiro (2016) have shown that the receipt of a fixed monthly income resulted in a short-term increase in self-reported welfare among beneficiaries in Kenya [25]. A review summarized the causal evidence and mechanisms for the relationship between poverty and common mental illnesses [5]. Poverty can increase exposure to factors that lead to poor mental health, such as economic tension and family violence. Poverty may also be a barrier to accessing goods, resources and services (which can make it impossible to satisfy even basic needs), contributing to the sense of social injustice generated from inequities in access [22]. Therefore, cash transfers could increase the welfare of beneficiaries by providing greater financial stability, as well as improving family members mental health.

We hypothesize that a socioeconomic intervention, Bolsa Família Program (BFP), could be associated with better mental health outcomes among youth, by mitigating some social drivers for poor mental health, such as exposure to violence [14]. Similarly, the possible BFP effect could be mediated by the reduction of important risk factors for mental illness among youth, parents’ mental illness and school dropout because of child labor. All testable variables in our datasets. By decreasing impulsivity, measured by hospitalizations from injuries, BFP could decrease attempted suicides and suicide cases among youth (Fig 1).

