**Fig 1 pone.0272481.g001:**
[figure not shown]
Potential mechanisms and pathways through which Bolsa Familia Program (BFP) may affect mental health-related hospitalizations and suicide among children and youth.

Therefore, the main potential mechanisms this project will test, through which BFP may be associated with better mental health outcomes are: (i) by reducing parental mental illnesses and family separations; (ii) by improving school retention (BFP has conditionalities related to education and health); (iii) by reducing exposure to violence; and finally, (iv) by decreasing impulsivity (Fig 1).

This protocol offers a unique opportunity to test these mechanisms in a countrywide dataset, and allows subgroup analyses. Considering that the impact of those factors may happen differently among more vulnerable groups, such as black youth, women, youth with lower income and living in deprived areas, after examining the impact of cash transfers on interrupting the pathways between poverty and poor mental health through one or more mechanisms previously mentioned (e.g., improving educational outcomes, reducing impulsivity, etc). We will then evaluate the differential impact of BFP across race and gender, and how this might be explained by the mechanisms. If the effect of the cash transfer is stronger among minorities, decreasing inequalities, it can also be one of the mechanisms through which this program may improve youth mental health.

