**Fig 2 pone.0272481.g002:**
[figure not shown]
Flowchart of non-beneficiary (non-BFP) and beneficiary of the Bolsa Familia Program (BFP) to test the association between BFP and youth mental health-related hospitalizations and suicide.

**Table 1 pone.0272481.t001:** Summary of the dataset’s description, from 2001 to 2018.

Dataset	Description	Sample	Variables of interest
The 100 Million Brazilian Cohort Baseline^70,73^	It was built from socioeconomic and demographic information of individuals applying for social benefits in Cadastro Unico (CadÚnico). CadÚnico is an extensive questionnaire with information on the household and on each individual.	114 million Brazilian cohort, including 66,079,181 Bolsa Familia Program beneficiaries and 47,928,524 non-beneficiaries. Among them 41,764,126, youth aged from 5–24 years old in the day of registration.	Demographic and socioeconomic variables (sex, age, ethnicity, education, work), conditions of the household (type of residence, material of household, household density, household supply, garbage destination etc), Health Care utilization, Institutional and community support (participation in groups, access to Social Assistance Reference Center, etc.) and Brazilian government social protection programs (BFP, etc).
Mortality Information System (SIM)^74,75,72^	The national system aimed to collect information on all deaths in Brazil death certificates. All deaths are recorded using a national standardized form and causes of death are registered according to the updated International Classification of Diseases CID-10.	All mortality cause (n = 21,313,290), including suicide (n = 181,527).	Demographic and socioeconomic variables (sex, age, ethnicity, education, work), place the death took place and primary and secondaries causes of death.
Hospital Information System (SIHSUS)^1^	All hospitalizations admissions financed by the Brazilian National Health System are recorded in this system. It includes about 80% of the Brazilian populations, approximately 150 million people	Hospitalizations from mental illness 5,478,980, including: 1,698,663 from alcohol and substance use-related disorders; 1,952,605 from schizophrenia; 832,974 due mood disorders, etc.	Identification and qualification of the patient, procedures, examinations, and medical acts performed, diagnosis, reasons for discharge, amounts due etc.

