We will apply methods from the SEM group, to specify and test the paths laid out in Fig 1. SEM will be used to fit models to the specifications in Fig 1 to allow a judgement on which models best fit our data, therefore allowing the identification of the model, which might be the closest to the causal paths underlying the relationship between exposure and outcome, including potential confounders. Estimation is performed either by Maximum Likelihood. Besides identification of the best fitting models, SEM allows detailing the relationship between indicators (variables) included in the models. After deciding which models are optimal, the particular coefficient estimates are calculated, which can be of fundamental importance to the identification of the intermediate nodes that have the highest influence on the outcome, or which act as mediators or moderators. Mediators are useful representations of confounders, and as long as the path coefficients are calculated, one can precisely estimate the effects resulting from the mediator.

Aim 4: Investigate early life exposures, intergenerational aspects, and to forecast scenarios in Brazil until 2030 using microsimulation models.

Finally, to match this aim we will examine: timing of the intervention in the life course, e.g., if cash transfer delivered earlier in life (e.g., in 2004 when an adolescent was 14 years old) will be associated with lower mental health-related hospitalizations and lower suicide rates 10 years later (when the same adolescent will be 24 years old); and whether mental health-related problems such as suicidality, post-traumatic stress disorder (PTSD), violent behavior passes over to second generations; and, furthermore to forecast scenarios of mental health-related hospitalizations and suicide rates using microsimulation models. This will leverage the results from previous objectives and compare the impact of different BFP implementations on mental health-related hospitalizations and suicide in Brazil until 2030.

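### Injury admissions stand in for impulsivity, the support offered concerns a different kind of proxy, and the path labelled impulsivity cannot be read as impulsivity whether it comes out small or large

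*Protocol article*

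**What the plan says.** The Conceptual framework defines the measure and the hypothesis together: "By decreasing impulsivity, measured by hospitalizations from injuries, BFP could decrease attempted suicides and suicide cases among youth". Impulsivity is the fourth mechanism there and is one of the four named in the second aim (Background).

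Data and measures lists the record as "G) physical injuries (228,278" for 2001–2018. Table 1 gives the youth denominator: "Among them 41,764,126, youth aged from 5–24 years old in the day of registration". Under Aim 1 in the Analytic strategy, physical injuries are also outcome (G), beside attempted suicide (H) and suicide (I).

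For Aims 2 and 3 the mechanisms are tested by regression discontinuity, propensity score matching and structural equation models (SEM). Path coefficients from the SEM are said to help with "identification of the intermediate nodes that have the highest influence on the outcome".

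The Discussion names as a possible limitation "The use of proxy in one of the four mechanisms proposed, physical injuries for impulsivity". It gives two answers: that such assessments "often depend on information from proxy informants, have been evaluated as robust", and that adjusting for health care access makes large differences between exposed and unexposed unlikely.

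**The concern.** The limitation is raised but not answered. Evidence about informants would support asking a relative about a young person's impulsiveness. As described, it says nothing about whether an injury admission reflects impulsiveness. Adjusting for health care access addresses unequal capture between beneficiaries and non-beneficiaries, which is a separate question from what the record measures.

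The record is also rare. A change in impulsivity that does not end in admission is not seen, and in a mediation model that unseen part moves into the path not attributed to impulsivity. What is at stake is the conclusion of Aim 2 on mechanism (iv), and any comparison of its coefficient with those of the other mechanisms.

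**Working it through.** The article gives no injury proportion, power figure or mediated effect, so there is no stated result to reproduce.

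**1. Share of youth who can be positive.** Inputs are 228,278 injury admissions (Data and measures) and 41,764,126 youth (Table 1).

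- 228,278 / 41,764,126 = 0.547%, so at least 99.45% score zero.
- This is an upper bound. It takes every admission as a different cohort youth, but the count is not labelled as youth-only or as linked to the cohort. The mood-disorder count beside it (832,974) equals the whole-system hospital count in Table 1, so the injury count is probably system-wide too.
- If half or a quarter of the admissions were youth, 99.73% or 99.86% would score zero.

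**2. Is the program-to-injury effect forced to null?** Power = Φ(√(d·π(1−π))·|ln RR| − 1.96), two-sided 0.05 (assumed). Here d is the number of events and π = 66,079,181 / 114,007,705 = 0.58, the whole-cohort beneficiary share, applied to youth as an assumption. Events are treated as independent.

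| Events | RR | Power |
|---|---|---|
| 228,278 | 0.99 | 0.66 |
| 228,278 | 0.95 | 1.00 |
| one quarter | 0.95 | 1.00 |
| 1% (a narrow window, 50:50, assumed) | 0.95 | 0.23 |
| 1% (same) | 0.90 | 0.71 |

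This path is well powered in the full cohort and loses power only in a narrow subset.

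**3. How much of the outcome can pass through injuries?** For a binary mediator with prevalence p, program effect RRa on the mediator and mediator effect RRb on the outcome, without interaction, the reduction is p(1−RRa)(RRb−1) / [1 + p(RRb−1)]. Take p = 0.547%. RRa and RRb are assumed, because the article gives neither.

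| RRb | Reduction at RRa = 0.8 | Ceiling at RRa = 0 |
|---|---|---|
| 2 | 0.11% | 0.54% |
| 5 | 0.43% | 2.1% |
| 10 | 0.94% | 4.7% |
| 20 | 1.9% | 9.4% |
| 50 | 4.2% | 21% |

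**4. How much of an impulsivity effect does the proxy recover?** Take the case kindest to the proxy: only impulsive youth have injury admissions, and each admission is a different youth. Assume that 10% are impulsive, that impulsivity carries a relative risk of 3, and that the program cuts it by 20%.

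- True reduction: 1 − (1 + 0.08×2)/(1 + 0.10×2) = 1 − 1.16/1.20 = 3.3%.
- Sensitivity of the proxy: 0.547% / 10% = 5.5%.
- Impulsive share among proxy-negatives without the program: (0.10 − 0.00547)/(1 − 0.00547) = 9.5%, so their risk is 1 + 2×0.095 = 1.19 and the apparent RRb is 3/1.19 = 2.52.
- Apparent reduction: 0.00547×0.2×1.52 / (1 + 0.00547×1.52) = 0.16%. With the risks taken in beneficiaries (proxy-negatives 1.15) it is 0.00547×0.2×(3−1.15) / [1.15 + 0.00547×(3−1.15)] = 0.17%.

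The proxy recovers about 5% of the true indirect effect. With impulsivity in 5% or 20% of youth and a relative risk of 3 to 10, the same steps give about 11% and about 2.5%.

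**5. Bias in the other direction.** Injuries from violence would overlap with mechanism (iii). Injuries from self-harm would overlap with outcome (H). Either could raise the injury-to-outcome coefficient for reasons other than impulsivity. The article gives no counts from which to size this.

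**The case against.** The article discloses the proxy and lists it as a limitation. The cited source cannot be seen, so only the sentence as worded can be faulted. An article may leave a misclassification analysis to an analysis plan that is not shown. The relative risks and prevalences above are assumed, and a very strong injury-to-outcome association (RR 20 to 50) would let a larger effect through. All of this stands. It does not repair the argument given for the measure, which answers a different question.

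A reader might go further on five points that the document does not support:

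- *A near-null result is built in.* Step 2 shows that rarity does not force the program-to-injury path to null. If admissions miss many impulsive youth but are specific, that ratio stays largely unbiased. The loss is in the mediated share, and overlap could push the path upward.
- *A null would be reported as impulsivity not being a pathway.* The article gives no rule for reading a null.
- *The SEM text ranks mechanisms by coefficient.* It describes what such models can show and sets no decision rule.
- *Record counts for the other mechanisms show that the comparison is distorted.* Those counts are system-wide totals. They are not counts for parents or youth in the cohort, and school retention has none.
- *The statement that one mechanism of four uses a proxy is wrong.* A psychiatric admission or a violence notification records its own construct incompletely. An injury admission stands in for a different construct, so the statement is defensible.

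**Conclusion.** The point holds in limited form. Neither defence in the Discussion shows that an injury admission measures impulsivity. At most 0.55% of youth can be positive, an upper bound from the article's own counts. Even with perfect specificity, the indirect effect would recover roughly 2.5% to 11% of an effect through impulsivity over the assumed range. Overlap with violence and attempted suicide could bias the path upward by an amount that cannot be sized here. A small coefficient therefore does not count against impulsivity, and a large one does not establish it. The program's effect on injury admissions, read as that and nothing more, is not in question.

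**What to change.** 1. In the Discussion, remove the informant sentence as support for the proxy, and say that adjustment for health care access addresses unequal capture only.
2. In the aims (Background) and the Conceptual framework, label mechanism (iv) as injury hospitalization (proxy for impulsivity). State that a null or small indirect effect does not exclude impulsivity.
3. Add, in the protocol or the analysis plan, a misclassification sensitivity analysis of the indirect effect over a stated range of proxy sensitivity and specificity.
4. Where the Analytic strategy uses path coefficients to find the most influential nodes, do not compare mechanism (iv) with the others without that correction.

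The cost is some rewording, one further analysis on data already held, and a weaker stated claim about impulsivity.
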